### VRQL

A translated, Chinese version of the National Eye Institute Visual Function Questionnaire-25 (NEI-VFQ-25) will be administered preoperatively, as well as at months 6 and 12.

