### Eligibility criteria {10}

The following are the criteria for the inclusion of candidates: (1) ≥ 18 years of age; (2) patients and their families fully understand the research and must sign an informed consent form; (3) diagnosed with type 1 or 2 diabetes mellitus; (4) hemoglobin A1c (HbA1c) levels of < 10% within 3 months; (5) moderate or severe nonproliferative diabetic retinopathy (NPDR) and proliferative diabetic retinopathy (PDR) without vitreous/preretinal hemorrhage [33]; (6) clear media for adequate OCT and OCTA images; (7) treatment-naïve DME diagnosed clinically; (8) CST of > 300 μm; (9) Early Treatment Diabetic Retinopathy Study (ETDRS) BCVA between 24 and 73 letters on the day of randomization; (10) treatment within 12 months of DME diagnosis; (11) no contraindication of vitrectomy or conbercept intravitreal injection. Each participant will only have one eye examined. If both eyes are qualified, the researcher will decide which of the eyes will be included in this study.

Exclusion criteria include the following: (1) any previous DME treatment (i.e., anti-VEGF injections, intravitreal corticosteroid usage, or macular photocoagulation); (2) macular edema caused by other diseases (i.e., age-related macular degeneration, retinal vein occlusion); (3) any previous intraocular surgeries (cataract surgery performed at least three months before study entry will not be exclusionary); (4) vision loss caused by other ocular diseases (i.e., glaucoma, high myopia); (5) a follow-up duration of < 12 months; (6) severe dysfunction of the heart, liver, kidney, lung, or other organs.

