### Relevant concomitant care permitted or prohibited during the trial {11d}

Treatment other than “Further intervention” will be prohibited, while treatment for the fellow eye and management of systemic diseases will be permitted.

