#### Secondary outcomes

The secondary outcomes include the changes in BCVA and CST from baseline to months 1, 3, and 6; assessment of SRF, location and size of cystoid change, continuity of the IS-OS layer, and presence and quantity of HRF in OCT at months 1, 3, 6, and 12; assessment of FAZ, superficial capillary density (sVD), and deep capillary density (dVD) in OCTA at months 3, 6, and 12; re-treatment and diabetic retinopathy (DR) development from baseline to month 12; cost-effectiveness analysis at month 12; and vision-related quality of life (VRQL) at months 6 and 12.

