### Sample size {14}

The sample size is estimated by the change of BCVA using PASS 15.0 (PASS 15.0.5 NCSS, LLC, USA). According to a published paper [9], mean BCVA change of IVC from baseline to month 12 was 8.2 ± 9.5 ETDRS letters. The maximum difference of 5 ETDRS letters was chosen for non-inferiority margin between groups. The sample size was calculated based on α level of 0.05 and *β* level of 0.2, N1 = N2 = 46. Then, the ultimate sample size is 102 (51 of each group) assuming a 10% dropout rate.

The non-inferiority margin was chosen because 5 ETDRS letters is considered clinical insignificant in practice. And the sample size is also sufficient for analysis of the change of CST based on previous studies [9, 36] (364 ± 88.6 μm and 200 ± 210 μm for IVC and vitrectomy combined with ILM peeling respectively).

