### Statistical methods

#### Statistical methods for primary and secondary outcomes {20a}

Descriptive statistics will be used to summarize study results and demographic variables. Means and standard deviations will be used to describe the normally distributed data, and medians and interquartile ranges will be used for non-normally distributed data. Categorical variables will be described as percentage and frequency. The two-sample *t*-test or Kruskal–Wallis test will be used to assess continuous variables, while the chi-square test will be used to evaluate categorical variables. A two-sided *p* value of less than 0.05 will be considered statistical significance. Besides, the records of patients with missing data will be deleted to ensure the accuracy of the results. All the data will be analyzed by SPSS 25.0 (Chicago, IL, USA).

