### Methods for additional analyses (e.g., subgroup analyses) {20b}

Regression analysis will be used for adjusted analysis to control for confounding factors.

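### The main NEI-VFQ-25 comparison is an unadjusted two-sample test of a person-level score; regression on the baseline score already collected would recover precision at no cost

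*Protocol article*

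**What the plan says.** Secondary outcomes lists "vision-related quality of life (VRQL) at months 6 and 12". In the same sentence, BCVA and CST are defined as changes from baseline; VRQL is not. The VRQL section states that the "National Eye Institute Visual Function Questionnaire-25 (NEI-VFQ-25) will be administered preoperatively, as well as at months 6 and 12", and Table 1 schedules it at enrolment and at the same two visits.

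Eligibility criteria {10} says: "Each participant will only have one eye examined". It adds: "If both eyes are qualified, the researcher will decide which of the eyes will be included in this study". No rule refers to the better- or worse-seeing eye. The concomitant-care section {11d} says that "treatment for the fellow eye and management of systemic diseases will be permitted".

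Statistical methods {20a} names the main comparison: "The two-sample *t*-test or Kruskal–Wallis test will be used to assess continuous variables". Methods for additional analyses {20b} adds one sentence: "Regression analysis will be used for adjusted analysis to control for confounding factors". It names no outcome and no covariate.

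**The concern.** The two treatments differ in one eye, but the questionnaire is answered by a person who sees with both. Variation in the fellow eye's vision and treatment enters the score and has nothing to do with the study-eye contrast. A plain two-sample test leaves all of that variation in the error term, together with the stable differences between people that a baseline score would absorb.

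VRQL is the only patient-reported outcome listed, and the rationale rests heavily on patient burden. The trial is framed as non-inferiority, yet VRQL has neither a margin nor a power statement. In that setting an imprecise null result is easily taken to mean that surgery is as good for quality of life. The article does not plan to read it that way, but nothing in it warns against doing so.

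**Working it through.** **What the sample size covers.** Sample size {14} gives "The sample size was calculated based on α level of 0.05 and *β* level of 0.2, N1 = N2 = 46", from a BCVA change SD of 9.5 letters and a margin of 5 letters. With a true difference of zero and one-sided α = 0.05:

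n = 2 × (1.645 + 0.842)² × 9.5² / 5² ≈ 44.6, so 45 per arm by the normal formula, and 46 with the noncentral t (power 0.805).

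The 46 therefore reproduces, and 46 × 1.10 = 50.6 gives the stated 51 per arm. The figure concerns BCVA alone. The article gives no SD, expected difference, margin or power for NEI-VFQ-25, so neither the precision of the VRQL comparison nor the fellow eye's influence on it can be computed.

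**What the baseline score is worth.** Let r be the correlation between baseline and follow-up score, with equal SDs at both times (assumption). In units of the follow-up score variance, the error variance is:

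- month score alone: 1
- change from baseline: 2(1 − r)
- regression on arm and baseline: 1 − r²

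| r (assumed) | month score | change | regression |
|---|---|---|---|
| 0.3 | 1 | 1.40 | 0.91 |
| 0.5 | 1 | 1.00 | 0.75 |
| 0.7 | 1 | 0.60 | 0.51 |

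The article does not say whether the two-sample test would use month scores or changes. In this table regression has the smallest error variance either way.

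**The same gain as power, for illustration only.** Take 46 per arm, two-sided 0.05, and an effect that an unadjusted test would detect with 80% power: (1.960 + 0.842) × √(2/46) = 0.584 SD. Adjustment divides the SD by a factor through √(1 − r²), and power becomes 0.836, 0.899 and 0.975 at r = 0.3, 0.5 and 0.7.

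**What adjustment does not do.** Suppose the study eye carries only a share w of the effect on the score (assumption; the article gives no eye weighting).

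| w (assumed) | power, unadjusted | power, adjusted, r = 0.5 |
|---|---|---|
| 1 | 0.800 | 0.899 |
| 0.75 | 0.556 | 0.679 |
| 0.5 | 0.288 | 0.366 |

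Adjustment raises power on every line, but the effect being estimated is still w × 0.584 SD. A covariate removes noise; it does not restore the share of the effect that the fellow eye masks.

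**The case against.** The strongest reply is that nothing said about VRQL is wrong. Covariate lists and data-capture items are commonly left to a full protocol or SAP, neither of which is shown. Regression is promised in {20b}. Section {20a} lists generic tests without mentioning VRQL, and a baseline questionnaire that is scheduled will presumably be used. Much of this stands: no contradiction is shown, and silence about fellow-eye covariates would not by itself be a finding. What remains is that the article does choose a main test for continuous outcomes. That test is unadjusted, and the regression sits under additional analyses without a named outcome or covariate.

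A second reply is that a person-level effect is a legitimate target: whether treating one eye changes the patient's quality of life is a fair question, and a small effect may be the true answer. That also stands, and it is a reason to label the outcome correctly.

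A reader might infer more: that the fellow eye biases the comparison, or that dilution is so strong that several times as many patients would be needed. The documents do not support either.

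- Allocation is randomised 1:1, so baseline fellow-eye status is balanced in expectation. Later fellow-eye treatment could differ by arm in an open-label trial, but nothing shows that it will.
- Any sample-size multiplier needs an assumption about which eye drives the score, such as the better-seeing eye alone. The article supplies none. It would also presuppose power for VRQL, which the plan never claims.
- The rule for the case where both eyes qualify is a contingency. It is not evidence of how often disease is bilateral.

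**Conclusion.** The point holds as a minor one about analysis choice. A person-level score that partly reflects an eye outside the trial is compared by an unadjusted test, although a baseline measurement of the same score is already scheduled. The cost is lost precision in an unpowered secondary outcome. It is not baseline bias, and it does not touch the BCVA or CST conclusions.

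The size cannot be derived from the article. On the assumed range r = 0.3 to 0.7, regression leaves 0.91 to 0.51 of the variance of a month-score comparison. The power figures are illustrations and say nothing about the power this trial has for VRQL.

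**What to change.** 1. Make the main VRQL analysis at months 6 and 12 a linear regression of the NEI-VFQ-25 score on arm with baseline NEI-VFQ-25 as covariate, reporting the adjusted difference with its confidence interval. If scores are markedly skewed, use robust standard errors rather than revert to an unadjusted test.
2. Add baseline fellow-eye BCVA as a covariate where it is measured at screening. The eligibility text does not guarantee it for everyone: a fellow eye that fails another criterion may not have been tested. Participants without it should stay in the analysis.
3. Record fellow-eye treatment during follow-up and tabulate it by arm, descriptively. It arises after randomisation and should not be a covariate.
4. State that VRQL is a person-level effect of treating one eye, and that a null result does not show equivalence. Do not present adjustment as removing dilution.
5. Keep any summary in participants whose study eye was the better-seeing one at baseline descriptive, since the subset may be small.

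The first and fourth items are wording only and use data already scheduled. The others require retaining a screening value where it exists and logging fellow-eye treatment at existing visits. No visit is added. The article states that recruitment had not started, so all of this can be fixed before any data are seen.

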### Plans to promote participant retention and complete follow-up {18b}

Investigators will give participants a detailed account of the follow-up timepoints and emphasize the importance of regular participation. Besides, investigators will supplement with frequent reminders and flexible scheduling options.

### Data management {19}

Electronic Data Capture (EDC) system will be used for data entry. Only authorized researchers will have access to and be able to process the data. Encryption technology will be used to protect data during transmission and storage. The data will be stored on secure servers and databases, which will be subject to strict access control and monitoring to ensure data confidentiality and integrity.

### Confidentiality {27}

All data collected will be coded, and patient identifiers will be removed to maintain anonymity. Electronic data will be stored in a secure, password-protected database accessible only to members of the research team. Paper documents will be kept in a locked cabinet to prevent unauthorized access.

### Plans for collection, laboratory evaluation, and storage of biological specimens for genetic or molecular analysis in this trial/future use {33}

Not applicable. There are no biological specimens.

### Statistical methods

#### Statistical methods for primary and secondary outcomes {20a}

Descriptive statistics will be used to summarize study results and demographic variables. Means and standard deviations will be used to describe the normally distributed data, and medians and interquartile ranges will be used for non-normally distributed data. Categorical variables will be described as percentage and frequency. The two-sample *t*-test or Kruskal–Wallis test will be used to assess continuous variables, while the chi-square test will be used to evaluate categorical variables. A two-sided *p* value of less than 0.05 will be considered statistical significance. Besides, the records of patients with missing data will be deleted to ensure the accuracy of the results. All the data will be analyzed by SPSS 25.0 (Chicago, IL, USA).

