### Outcomes {12}

#### Primary outcome

The primary outcome is the changes in BCVA and CST from baseline to month 12 between the two groups.

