### Assignment of interventions: allocation

#### Sequence generation {16a}

One hundred and two random numbers will be generated by computer-generated algorithm (SPSS software), and the corresponding participants will be evenly distributed to the study group (the first 51 numbers) and the control group (the last 51 numbers) according to the random number sequence.

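### The primary month-12 changes in BCVA and CST are compared without adjusting for baseline, which gives up precision in the non-inferiority comparison at no saving

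*Protocol article*

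**What the plan says.** The Primary outcome section reads "The primary outcome is the changes in BCVA and CST from baseline to month 12 between the two groups". Under Statistical methods for primary and secondary outcomes {20a}, the method for such variables is fixed: "The two-sample *t*-test or Kruskal–Wallis test will be used to assess continuous variables, while the chi-square test will be used to evaluate categorical variables". No covariate is named there.

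Both baseline values will exist. The eligibility criteria require a BCVA of 24 to 73 letters on the day of randomization, and Table 1 schedules BCVA and OCT at enrollment for everyone. Sequence generation {16a} describes one list of random numbers, with no stratification on either measure.

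Adjustment is mentioned once, under additional analyses {20b}: "Regression analysis will be used for adjusted analysis to control for confounding factors". That sentence names no outcome and no covariate, and gives the regression no role in the non-inferiority decision.

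The Sample size section {14} supplies the design figures. They are "mean BCVA change of IVC from baseline to month 12 was 8.2 ± 9.5 ETDRS letters" and "The maximum difference of 5 ETDRS letters was chosen for non-inferiority margin between groups", with α 0.05, β 0.2, 46 per group, and 51 per group after allowing for dropout.

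**The concern.** Subtracting the baseline is not the same as adjusting for it. A change score fixes the slope of the month-12 value on baseline at 1. If the true slope is below 1, eyes that enter with worse values tend to improve more, and two things follow. Variance that the baseline could explain stays in the error term, so the interval for the treatment difference is wider than the data require. And a fraction of any chance baseline difference between arms, equal to 1 minus the slope, stays in the estimated treatment effect, in either direction.

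Both matter here because the conclusion depends on where one interval for the BCVA difference lies relative to 5 letters, with about 46 evaluable eyes per arm, a wide entry range and no stratification. The rank-based alternative adds a separate difficulty: Kruskal–Wallis tests ranks and yields no difference in mean letters to compare with a margin stated in letters.

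**Working it through.** **Inputs from the article (Sample size {14}).** SD of BCVA change 9.5 letters, margin 5 letters, 46 evaluable per arm. The true difference is taken as 0 and the SD as common to both arms.

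**Reproducing the plan's figure.** The standard error of the difference is 9.5 × √(2/46) = 1.98, so the noncentrality is 5/1.98 = 2.52. With the noncentral t distribution on 90 degrees of freedom, power at one-sided 0.05 is 80.5%, and 46 is the smallest n per arm that reaches 80%. At one-sided 0.025 the requirement would be 58 per arm, so the stated 46 corresponds to one-sided 0.05.

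**Effect of adjustment, equal SDs.** Let s be the SD at both times and ρ the correlation between baseline and month 12. The article gives neither, so both are assumptions.

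- Variance of change: 2s²(1 − ρ)
- Residual variance under ANCOVA: s²(1 − ρ²)
- Ratio: (1 + ρ)/2, so the effective SD is 9.5 × √((1 + ρ)/2)

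| ρ | Effective SD | Power, one-sided 0.05 | Gain (points) | Gain at one-sided 0.025 |
|---|---|---|---|---|
| none (unadjusted) | 9.50 | 80.5% | – | (70.4% unadjusted) |
| 0.3 | 7.66 | 92.8% | 12.3 | 16.8 |
| 0.5 | 8.23 | 89.4% | 8.9 | 11.8 |
| 0.7 | 8.76 | 85.8% | 5.3 | 6.9 |
| 0.8 | 9.01 | 84.0% | 3.5 | 4.5 |

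**Tying ρ to a baseline SD.** With equal SDs, a change SD of 9.5 implies ρ = 1 − 9.5²/(2s²).

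- s = 9.5 gives ρ = 0.50.
- s = 12 gives ρ = 1 − 90.25/288 = 0.69 and a gain of 5.5 points.
- s = 14 gives ρ = 1 − 90.25/392 = 0.77 and a gain of 4.1 points.

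The values 12 and 14 are assumptions. For scale, an even spread over 24 to 73 letters has SD 49/√12 = 14.1.

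**Unequal SDs.** Entry BCVA is restricted to 24–73 letters and month-12 BCVA is not, so the later SD may be the larger. Let k be the ratio of month-12 to baseline SD. The slope is ρk, and the variance removed by adjustment is (1 − ρk)² times the baseline variance. Holding the change SD at 9.5, at one-sided 0.05:

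- k = 1.2: gain 4.6 points at ρ 0.5, 2.7 at ρ 0.6 and 1.2 at ρ 0.7.
- k = 1.3: gain 3.1 points at ρ 0.5 and 0.3 at ρ 0.7.

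**Chance imbalance.** With a baseline SD of 12, the standard error of the between-arm baseline difference is 12 × √(2/46) = 2.50 letters. With equal SDs the slope is 0.69, so an imbalance of one standard error shifts the unadjusted difference by 0.31 × 2.50 = 0.8 letters, or 0.8/5 = 16% of the margin.

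**CST.** The article gives no CST margin and no baseline-to-follow-up correlation, so the corresponding calculation cannot be done.

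**The case against.** The strongest reply is that nothing promised is lost. The trial was sized on the SD of change, which is the right input for an unadjusted comparison of changes, and that comparison has the stated power. The t-test is valid and is unbiased over repeated randomization. This stands: the point is about efficiency and does not identify an error.

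A second reply is that {20b} already plans an adjusted regression, and that its details belong in an analysis plan that is not shown. It stands in part. Adjustment is not absent and missing covariate detail is no fault in an article. But {20a} does fix the method for the primary outcome, and {20b} places the regression outside it.

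A third reply is that the size of the gain is unknown. This stands too. A reader might infer that the plan discards about nine points of power. That figure needs ρ = 0.5 and equal SDs, neither of which the article gives, and it implies a baseline SD of 9.5 letters. A wider baseline or a more variable month-12 value makes the gain smaller, possibly negligible.

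A reader might also take the 70.4% at one-sided 0.025 as a consequence of not adjusting. It is not. It comes from sizing that reproduces only at one-sided 0.05, set beside the {20a} rule "A two-sided *p* value of less than 0.05 will be considered statistical significance", which is a separate matter.

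**Conclusion.** The point holds as lost precision and avoidable exposure to chance imbalance in the primary comparison. The documents do not support calling the t-test invalid, biased or short of its planned power.

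For BCVA the gain from adjustment is about 3.5 to 12 points of power for ρ from 0.8 down to 0.3, given equal SDs, 46 per arm and one-sided 0.05. It is about 4 to 5.5 points if the baseline SD is 12 to 14 letters, and near zero if the slope nears 1. The shift of about 0.8 letters per standard error of imbalance rests on a baseline SD of 12 and equal SDs. The argument for adjustment applies to CST in principle, but no size can be attached to it. The objection to Kruskal–Wallis needs no assumption: it cannot supply the interval that a 5-letter margin calls for.

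This is a worthwhile, essentially free improvement.

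**What to change.** In {20a}, name ANCOVA as the primary analysis: month-12 change in BCVA regressed on treatment group and baseline BCVA, with the confidence interval for the adjusted difference (PPV minus IVC) compared with −5 letters. Use the same model for CST with baseline CST as the covariate. Keep the unadjusted comparison as supportive, and state that the {20b} regression is secondary to this model.

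The cost is a wording change and one degree of freedom. No new data, visits or participants are needed. The Trial status section says that recruitment has not started, so the change can be prespecified before any outcome is seen.

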### Trial design {8}

VVV is a single-center, prospective, parallel-group, non-inferiority, randomized controlled trial. Enrolled patients will be randomly assigned at a 1:1 ratio into the study group (PPV combined with ILM peeling) and control group (IVC), and a follow-up period of 12 months is planned. Interim analyses will not be conducted. Figure 1 depicts the trial design flow chart.

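### The analysis stated for the primary outcomes is a two-sided difference test that never uses the 5-letter non-inferiority margin and does not match the alpha behind 46 per arm

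*Protocol article*

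**What the plan says.** Trial design {8} fixes the framework: "VVV is a single-center, prospective, parallel-group, non-inferiority, randomized controlled trial". The Methods paragraph of the abstract says the same. Two outcomes share primary status: "The primary outcome is the changes in BCVA and CST from baseline to month 12 between the two groups".

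Sample size {14} rests on BCVA alone. It takes from a published study that "mean BCVA change of IVC from baseline to month 12 was 8.2 ± 9.5 ETDRS letters", and adds: "The maximum difference of 5 ETDRS letters was chosen for non-inferiority margin between groups". On error rates it says "The sample size was calculated based on α level of 0.05", without saying whether that is one-sided or two-sided. With β of 0.2 it arrives at 46 per arm, raised to 51 per arm (102 in total) for 10% dropout.

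The section on statistical methods for primary and secondary outcomes {20a} names the analysis. For continuous variables the two-sample t "test or Kruskal–Wallis test will be used to assess continuous variables, while the chi-square test will be used to evaluate categorical variables". Significance is a two-sided p value below 0.05.

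The section on additional analyses {20b} adds only this: "Regression analysis will be used for adjusted analysis to control for confounding factors". The margin appears in {14} and nowhere else. No section gives CST a margin.

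**The concern.** The design and the sample size ask whether PPV is worse than IVC by 5 letters or more. The stated test and its significance rule ask whether the two arms differ at all. A non-significant result on the second question does not settle the first, because it can come from imprecision as easily as from similarity.

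The Kruskal–Wallis branch is further from the goal. With two arms it is a rank test, and as named it returns a p value with no estimate in letters to set against 5. An interval in letters would need a further method that the article does not name.

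The comparison is surgery against what the Background calls first-line therapy. If the decision rule is left open, the conclusion could rest on whichever summary is at hand when the data are read, and one available summary (p above 0.05) has poor error control at the margin.

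**Working it through.** **Inputs.** From {14}: margin 5 letters, SD 9.5, α 0.05, β 0.2, 46 evaluable per arm, 51 randomised per arm. From {8}: 1:1 allocation. Assumptions: a true difference of 0 for the sample size (not stated in the article) and the same SD in both arms.

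**Step 1: reproduce the plan's figure.** For a test against the margin, the normal approximation is

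n per arm = 2 × (z₁₋α + z₁₋β)² × SD² / margin²

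- One-sided 0.05: 2 × (1.645 + 0.842)² × 9.5² / 5² = 44.6, so 45. The exact noncentral-t version gives 46, the plan's figure.
- One-sided 0.025: 2 × (1.960 + 0.842)² × 9.5² / 5² = 56.7, so 57. The noncentral-t version gives 58.
- A two-sided 0.05 difference test to detect 5 letters also needs 57 (normal approximation).

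Of these, only the margin-based test at one-sided 0.05 reproduces 46. Section {14} therefore sizes one test at one error level, and {20a} names another test at another level.

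**Step 2: where the two rules part.** SE of the difference = 9.5 × √(2/46) = 1.98 letters. The 95% half-width is 3.94 and the 90% half-width is 3.29. At the planned SD:

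- The stated test is non-significant when the observed difference lies within ±3.94 letters.
- A 95% interval shows non-inferiority when the observed difference is above −5 + 3.94 = −1.06 letters.
- A 90% interval shows it when the observed difference is above −5 + 3.29 = −1.71 letters.

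An observed PPV deficit between 1.06 letters (1.71 with a 90% interval) and 3.94 letters is thus non-significant without showing non-inferiority.

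**Step 3: how often this matters.** Simulation of 200,000 trials with 46 per arm and SD 9.5:

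| True PPV minus IVC | Two-sided test non-significant | Non-inferior by 90% CI | Non-inferior by 95% CI |
|---|---|---|---|
| −5 (at the margin) | 29.6% | 5.0% | 2.5% |
| 0 (equal) | 95.0% | 80.5% | 70.5% |

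With equal arms, 27.0% of all trials are non-significant while the 95% interval still reaches −5 letters.

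**Step 4: power of a margin-based rule.** Noncentral t, true difference 0, SD 9.5, no covariate adjustment:

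| Evaluable per arm | 90% CI (one-sided 0.05) | 95% CI (one-sided 0.025) |
|---|---|---|
| 46 | 80.5% | 70.4% |
| 51 | 84.0% | 74.9% |

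**The case against.** The strongest reply is that {20a} is a generic paragraph in a condensed article. A two-sample t-test can be run against a shifted null and also yields a confidence interval for the mean difference, which can be set against −5 letters. The 46 per arm shows that the authors had the margin in mind, and an unseen analysis plan may hold the decision rule.

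Much of this stands. A reader might infer that the trial cannot show non-inferiority at all. The article does not support that: the t-test branch produces what is needed, and a significant result in favour of PPV would imply non-inferiority as well. A reader might also infer that p > 0.05 will be taken as proof of non-inferiority. No section says so, and the 30% figure applies only under that misreading.

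Two further inferences fail:

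- That the comparison ignores baseline vision. The outcome is change from baseline, so baseline is already subtracted, and an unadjusted comparison of change scores is valid in a randomised trial.
- That non-significance at a smaller true deficit, say 3 letters, shows false positives. A 3-letter deficit lies inside the margin, so a conclusion of non-inferiority there would be correct.

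What does not stand is the appeal to missing detail. Section {20a} is not silent. It names the tests for the primary outcomes and a significance rule, and these do not match {8} and {14}.

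**Conclusion.** The point holds as an inconsistency between sections. The article declares and sizes a non-inferiority trial on a 5-letter margin, but its stated rule for the primary outcomes never uses that margin. The two-sided 0.05 in {20a} does not match the one-sided 0.05 that yields 46 per arm, and the Kruskal–Wallis branch offers nothing on the letter scale.

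If the gap were filled by reading p > 0.05 as non-inferiority, the error at a true 5-letter deficit would be about 30%, against 5% or 2.5% for a margin-based rule with a 90% or 95% interval. These figures assume 46 evaluable per arm, SD 9.5 in both arms and roughly normal mean differences. The finding does not extend to a claim that the data could not support a non-inferiority conclusion, or that the unadjusted change-score comparison is invalid.

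**What to change.** In {20a}, state the following before any outcome data are analysed:

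1. **Decision rule for BCVA.** Non-inferiority is concluded if the lower confidence limit for the mean difference (PPV minus IVC) in BCVA change at month 12 is above −5 letters.
2. **Interval level.** A two-sided 90% interval (one-sided 0.05) agrees with {14}. If a 95% interval (one-sided 0.025) is chosen, {14} should give the unadjusted power as about 70% at 46 evaluable per arm (about 75% at 51) in place of 80%. Keeping 80% would need 58 evaluable per arm, or 58 / 0.9 = 64.4, so 65 randomised per arm and 130 in total.
3. **Model.** Take the interval from an ANCOVA with arm and baseline BCVA. This is a precision gain at no cost, not the repair of an error; the documents give no correlation from which to size the gain.
4. **Rank tests.** Do not use Kruskal–Wallis for the non-inferiority decision. It can remain for other comparisons.
5. **CST.** Say whether CST, which has no margin, is tested as a difference, and how it enters the trial's conclusion alongside BCVA.

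With a 90% interval the change is wording only, since BCVA is already measured at enrolment and month 12. With a 95% interval the cost is either a lower stated power or a larger sample. The article reports that recruitment has not started, so either choice could still be made in advance.
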